	**Episiotomy**					
		Mediolateral episiotomy, midline episiotomy, and intradermal suture	Mean (SD) or medians for continuous variables		Case report forms	
	**Apgar score**					
		Apgar scores in 1 minute, 5 minutes, and 10 minutes after birth	Mean (SD) or medians for continuous variables		Case report forms	
	**Admission to neonatal intensive care unit**					
		Newborn transferred to the neonatal intensive care unit because of any emergency	Mean (SD) or medians for continuous variables		Case report forms	

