#### Secondary Outcomes

Secondary outcomes will include the duration of the second stage of labor, maternal pushing position, mode of birth, rates of cesarean birth, perineal laceration, the rates of episiotomy, newborn Apgar scores, rates of newborn resuscitation, and rates of transfer to the neonatal intensive care unit. Table 5 illustrates the primary and secondary objectives, outcomes, criteria for success, methods for analysis, and measurement tools.

**Table 5 table5:** Primary and secondary outcome criteria, analysis, and measurement.

Objectives, outcomes, and criteria for success				Methods of analysis		Measurement or tool
**Primary objectives: To test the feasibility of a future RCT^a^ to compare the effects of spontaneous pushing and directed pushing for maternal and neonatal outcomes**						

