	**Mode of birth**					
		Normal vaginal birth, forceps extraction, vacuum extraction, breech delivery, and cesarean birth	n (%) for categorical variables		Case report forms	

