	**Neonatal resuscitation**					
		Resuscitation strategies following China Neonatal Resuscitation Guideline	Mean (SD) or medians for continuous variables		Case report forms	

^a^RCT: randomized controlled trial.

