### Data Analysis

The data in this study include both quantitative and qualitative data. For quantitative data, “intention-to-treat” analysis will be used. Statistical description will be conducted by the description of mean value, SD, number of cases, and percentage. Pearson chi-square test will be conducted for categorical variables. Independent group 2-tailed *t* test will be conducted for continuous variables. The threshold for statistical significance will be set at .05. For qualitative data, a framework method will be used, which is commonly applied for the thematic analysis of interview transcripts [30]. After a verbatim transcription of the audio recording, the framework method will help to create and apply an analytic framework in the data analysis process in 5 steps (data familiarization, framework identification, indexing, charting, mapping, and interpretation) [31]. The quantitative and qualitative data will be combined in order to compile recommendations from the feasibility in order to conduct a future RCT.

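### Table 5 classes episiotomy, NICU transfer and neonatal resuscitation as continuous variables, although the protocol defines all three as rates

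*Protocol article*

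**What the plan says.** - **Table 5, rows for episiotomy, NICU admission and neonatal resuscitation:** each has the same method entry, "Mean (SD) or medians for continuous variables". What is measured in these rows is, respectively, a list of episiotomy and suture types, whether the newborn was transferred, and the resuscitation strategies used.
- **Table 5, rows for mode of birth and perineal laceration:** the method is "n (%) for categorical variables".
- **Secondary Outcomes:** the list includes "the rates of episiotomy, newborn Apgar scores, rates of newborn resuscitation, and rates of transfer to the neonatal intensive care unit". The Case Report Form section repeats it for data extraction. The same Secondary Outcomes paragraph introduces Table 5 as the place that shows, among other things, the methods of analysis.
- **Data Analysis:** description is by mean, SD, number of cases and percentage. For testing, "Pearson chi-square test will be conducted for categorical variables", and continuous variables go to an independent two-sided t test at the .05 level. This section does not say which outcome belongs to which type.

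The Apgar row carries the continuous label too. An Apgar score is numeric, so that row is not part of this point.

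**The concern.** NICU transfer happens or does not. Episiotomy types and resuscitation strategies are unordered categories, and whether any was used is again yes or no. A table that labels them continuous contradicts the text that defines them as rates, and departs from the convention the same table follows for two comparable outcomes.

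The label matters because the Data Analysis section assigns methods by variable type, and Table 5 is the only place in the article that assigns a type to each outcome. An analyst who follows the table could report medians of yes/no data, or average arbitrary category codes. The study is meant to inform a future randomized trial, and for these outcomes that requires event proportions in each cohort.

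**Working it through.** **Inputs.** The cohort size is 105 per group (Sample Size Determination). The documents give no event rates for these outcomes, so every count below is an assumption chosen for illustration. The plan states no figure on this point that could be reproduced.

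**1. Median of a yes/no outcome.** With 105 births the median is the 53rd ordered value. It is 0 whenever 52 or fewer births have the event, that is, at any rate below 50%.

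| Assumed events, of 105 each | Rates | Medians |
|---|---|---|
| 42 vs 21 | 40.0% vs 20.0% | 0 vs 0 |
| 7 vs 1 | 6.7% vs 1.0% | 0 vs 0 |
| 10 vs 52 | 9.5% vs 49.5% | 0 vs 0 |

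For the first row the Pearson statistic is 210 × (42×84 − 21×63)² / (105×105×63×147) = 10.0, p = 0.0016. The medians show nothing of it.

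**2. Mean and t test of a 0/1 outcome.** The mean of a 0/1 variable is the event rate: 42/105 = 0.400, 7/105 = 0.067, 1/105 = 0.010. The t test and the uncorrected chi-square test nearly coincide:

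| Events | t test p | Chi-square p |
|---|---|---|
| 42 vs 21 | 0.0015 | 0.0016 |
| 7 vs 1 | 0.031 | 0.031 |
| 3 vs 10 | 0.0453 | 0.0450 |

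Over all 5,564 pairs of unequal counts examined at 105 per group, the two tests never disagreed at .05, and the largest difference in p was 0.0024. No rate or difference is lost by this route.

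**3. Mean of numeric category codes.** Assume none / mediolateral / midline / intradermal suture = 69/30/3/3 in one cohort and 84/6/9/6 in the other.

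- Codes 0, 1, 2, 3: means (30×1 + 3×2 + 3×3)/105 = 45/105 = 0.43 and (6×1 + 9×2 + 6×3)/105 = 42/105 = 0.40; t test p = 0.79.
- Codes for mediolateral and midline swapped: means (30×2 + 3×1 + 3×3)/105 = 72/105 = 0.69 and (6×2 + 9×1 + 6×3)/105 = 39/105 = 0.37; t test p = 0.013.
- Chi-square across the four categories, whatever the coding: p = 0.00008. (One expected count is (3 + 6)/2 = 4.5, so this p is approximate.)
- Any episiotomy entry, 36 vs 21 of 105: 34.3% vs 20.0%, chi-square p = 0.020.

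The same data give no difference or a clear one, depending only on the numbering.

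**4. Sparse events under the categorical test.** For 7 vs 1 the expected count is (7 + 1)/2 = 4 events per cohort. Pearson chi-square gives p = 0.031 and Fisher's exact test 0.065. Correcting the label therefore leaves the question of which categorical test suits rare neonatal events.

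**The case against.** The case for leaving this as a small slip is strong.

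- **Rates are planned elsewhere.** A reader might infer from Table 5 that the promised rates will not be produced. The documents do not support that: the Data Analysis section plans number of cases, percentage and a chi-square test for categorical variables, and the case report form is to collect these outcomes as rates. This stands.
- **A t test is not stated.** A reader might also infer that these outcomes will go to a t test and that real differences will be lost. Table 5 names no test. The t test follows only if its label is carried into the Data Analysis section, and step 2 shows that on 0/1 data it would hide nothing at this sample size. This stands too.
- **The harmful readings need further choices.** The cells offer a mean as well as a median, the Data Analysis section lists no medians, and no numeric coding of types or strategies is specified. So harm is possible, not certain.
- **Probable origin.** Four consecutive rows share the same text, which would fit a copied entry that suits only Apgar. The documents cannot confirm this, and the analyst would still have the wrong entry.
- **Limited stakes.** Effectiveness is a secondary objective, to be explored. No feasibility success criterion uses these rows, and the documents do not call NICU transfer or resuscitation safety endpoints.

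The objection narrows the consequence. It does not remove the contradiction between Table 5 and the outcome definitions.

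**Conclusion.** Wrong as written, with moderate to minor severity. Three rows of Table 5 give categorical outcomes a continuous method, against the outcome definitions and against the table's own convention. This is a stated method that is wrong, not detail left to a fuller document.

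The possible harm has two forms: medians that read 0 vs 0 at any pair of rates below 50%, and averaged codes whose result depends on the numbering. Both depend on how an analyst reads the cell, and the sizes shown rest on assumed counts at 105 per cohort. The documents do not support the stronger conclusions that rates will go unreported or that a t test of yes/no data would mask differences. The primary feasibility and acceptability outcomes are unaffected.

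**What to change.** 1. In the episiotomy, NICU admission and neonatal resuscitation rows of Table 5, replace the method entry with the one already used for mode of birth and perineal laceration: "n (%) for categorical variables".
2. Report each outcome as the proportion of births with the event (any episiotomy, any NICU transfer, any resuscitation). List episiotomy types and resuscitation strategies as counts.
3. Compare cohorts with the categorical test already named in the Data Analysis section, and add that an exact test is used where expected counts are below 5.
4. Optional: give a risk difference with a 95% confidence interval for each event.

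The cost is three table cells and one added sentence. No new data are needed, and the sample size does not change.

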	**Neonatal resuscitation**					
		Resuscitation strategies following China Neonatal Resuscitation Guideline	Mean (SD) or medians for continuous variables		Case report forms	

^a^RCT: randomized controlled trial.

### Data Collection

#### Overview

The primary and secondary outcomes will be measured using a combination of qualitative and quantitative methods. Three data collection tools will be used during this process.

#### Case Report Form

A self-designed case report form (CRF) will be used by the researcher (JY) to extract the effectiveness outcomes from a woman’s medical notes. These will include the duration of the second stage of labor, maternal pushing position, mode of birth, rates of cesarean birth, perineal laceration, rates of episiotomy, newborn Apgar scores, rates of newborn resuscitation, and rates of transfer to the neonatal intensive care unit. The researcher (JY) will also record on the work log the name of the midwife who supported the recruited woman with spontaneous pushing. As the maternal pushing position is not routinely recorded in medical notes, the researcher (JY) will ask the midwife about a woman’s pushing position during labor and will record it on the CRF. Midwives will also be advised to record the maternal pushing position in the labor notes during the preparation sessions.

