## Methods

### Study Design

This feasibility study is a nonrandomized, single-group, noninferiority trial. All participants will receive the intervention (spontaneous pushing). A mixed methods approach will be used to assess the primary and secondary outcomes. This protocol adheres to the SPIRIT (Standard Protocol Items: Recommendations for Intervention Trials) guidelines (Multimedia Appendix 1) [21].

Table 1 illustrates the objectives, outcomes, and the corresponding study design. Tables 2 and 3 illustrate the chart of the study designs, visits, and assessments for both women and midwives. The flow diagram (Multimedia Appendix 2) demonstrates the enrollment, allocation, follow-up, and assessment process for women to compare the effectiveness of the intervention.

**Table 1 table1:** Objectives, outcomes, and study design.

Objectives and outcomes		Study design
**Primary objective: To test the feasibility of a future RCT^a^ to compare the effects of spontaneous pushing and directed pushing for maternal and neonatal outcomes**		
	Feasibility: recruitment rates, retention rates, and attendance rates of participants	Quantitative study design
	Acceptability: women’s and midwives’ perspectives and acceptability of the intervention	Quantitative study design (survey for women) and qualitative design (interviews for midwives)
**Secondary objective: To explore the effectiveness of spontaneous pushing and directed pushing for women without an epidural during the second stage of labor**		
	Maternal and neonatal outcomes	Quantitative study design

^a^RCT: randomized controlled trial.

**Table 2 table2:** Chart of the study design, visits, and assessment for women.

Time point			Visit 1: during late pregnancy at clinics		Visit 2: at clinics or admission to the prenatal ward		Visit 3: during the second stage of labor		Visit 4: within 2 hours after birth		Visit 5: during the stay in the postnatal ward

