### Participants

All participants will be recruited from the Fourth Hospital of Shijiazhuang, Hebei Province, China. In total, 105 women will be recruited to receive the intervention. At the same time, 105 sets of medical notes will be identified, and relevant information will be extracted to compare health outcomes between the 2 cohorts. These medical notes will be from women who received standard care, that is, “directed pushing” during the second stage and met the same selection criteria as the women in the spontaneous pushing group. The women whose notes will be reviewed will not be recruited into this study, but permission has been obtained from the site-specific hospital to examine the deidentified medical notes. The demographic data, that is, age and the parity and labor care section of the medical notes will be reviewed and examined and parity in 2 cohorts will be matched for further comparison.

Six midwives will be recruited to support spontaneous pushing. They will be rostered to cover all 4 shifts of the roster to ensure that every recruited woman will be supported to push spontaneously by a recruited and trained midwife. All recruited midwives will be interviewed for the qualitative study part.

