### Eligibility Criteria

The eligibility criteria for women and midwives are presented in Textboxes 1 and 2. The medical note audit will include women who received directed pushing during the second stage of labor and met the same eligibility criteria as the women in the spontaneous pushing group.

Eligibility criteria for women.

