## Discussion

### Principal Findings

This is a protocol for a study assessing the feasibility, acceptability, and effectiveness of spontaneous pushing during the second stage of labor among Chinese women without epidural analgesia.

A challenge for this study may likely be the recruitment of laboring women. One of the exclusion criteria for women in this study is “administered epidural analgesia” (Table 3). A large proportion of recruited women may be excluded due to the use of epidural analgesia during labor. The epidural analgesia rate varies from one hospital to another in China [32]. However, the most recently noted rate within the study hospital was around 65% for primiparous women. Despite the anticipated high loss rate of laboring women, this exclusion criterion is set based on the underpinning midwifery philosophy that labor and birth under the use of epidural analgesia is not considered a physiological process. The International Confederation of Midwives [33] states that “Normal birth is where the woman commences, continues and completes labour with the infant being born spontaneously, in the vertex position at term, without any surgical, medical, or pharmaceutical intervention.” The use of epidural analgesia inhibits nerve conduction by blocking painful impulses from the nerves [34]. Although epidural analgesia is considered to be an effective way of pain relief in labor and birth [35], blocking of pain impulses also blocks other impulses conducted by the nerves, including pushing or bearing down urges. At the same time, the “intervention” in this study, spontaneous pushing, encourages laboring woman to feel their bodily urges and push in their most effective way. From this perspective, women who used epidural analgesia during labor may have difficulty feeling their pushing instinct, and hence, they are excluded from this study. The criteria of excluding women who used epidural during labor does not mean to influence women’s choices for their pain relief methods. The reasons for this criteria item will be explained beforehand to women to avoid their potential shame of the use of epidural analgesia during labor.

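### Second-stage duration is compared between nonrandomized cohorts matched on parity only, with induction, oxytocin and non-epidural analgesia not named for collection or adjustment

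*Protocol article*

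**What the plan says.** All references are to the protocol article.

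- **Design.** Study Design: "This feasibility study is a nonrandomized, single-group, noninferiority trial". Participants: the intervention group is 105 recruited women, each supported by one of six trained midwives. The comparison is 105 sets of notes from women who had directed pushing as routine care.
- **Comparability.** The comparison notes must come from women who "met the same eligibility criteria as the women in the spontaneous pushing group" (Eligibility Criteria). Participants adds that age, parity and the labor care section of the notes will be looked at, and that "parity in 2 cohorts will be matched for further comparison". No other matching variable is given.
- **Eligibility.** The only treatment named as an exclusion is epidural analgesia. Both cohorts must also have had an uncomplicated labor with no condition bearing on second-stage care.
- **Data items.** Case Report Form: the form serves to extract the effectiveness outcomes. "These will include the duration of the second stage of labor, maternal pushing position, mode of birth, rates of cesarean birth, perineal laceration", then episiotomy, Apgar scores, resuscitation and neonatal intensive care transfer.
- **Analysis.** Data Analysis: a two-tailed independent-groups t test for continuous variables and a Pearson chi-square test for categorical ones, at .05. No adjustment or stratification is mentioned.
- **Role of duration.** It is a secondary outcome. Sample Size Determination also makes it the basis of the 105 per group and says the study should supply estimates for the future trial's sample size.

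**The concern.** The two cohorts differ in more than pushing style. One consists of women who agreed in late pregnancy to try spontaneous pushing and were cared for by volunteer, specially trained midwives. The other is routine care. Use of induction, oxytocin augmentation or non-epidural analgesia could well differ between such groups, and these treatments could affect the length of the second stage. Oxytocin is the clearest case, because it acts on contractions.

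Taken together, the matching variable, the listed form items and the tests give a comparison in which these co-treatments are not balanced by design, not listed for capture and not adjusted for. If oxytocin shortens the second stage (an assumption; the article does not discuss it), lower use in the spontaneous group would make that group look slower, and higher use would hide a real lengthening. The result could be misread as an effect of pushing style and carried into the planning of the future trial.

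**Working it through.** **1. The plan's own figure.** Sample Size Determination gives 90% power, α = .05, 20% dropout and 105 per group. It gives no difference, SD or margin, so 105 cannot be reproduced from the stated inputs. Solving backwards:

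- Evaluable per group: 105 × 0.8 = 84.
- Two-sided .05: d = (1.960 + 1.282) × √(2/84) = 0.50 SD. One-sided .05: d = 0.45 SD.
- Forward check with an assumed d = 0.5: n = 85, and 85/0.8 rounds up to 107, close to 105.

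This shows only that 105 is plausible for a difference of about half an SD. That is the scale against which to judge a bias.

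**2. Standard error of the difference in SD units, √(2/n).** For n = 84 it is 0.154; for n = 105 it is 0.138.

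**3. Bias from one unbalanced co-treatment.** Bias = (difference in proportion treated) × (effect on duration in SD). The documents give neither quantity, so both are assumed: an imbalance of 10, 20 or 30 percentage points and an effect of 0.25, 0.5 or 0.75 SD. The last column is the chance that a two-sided .05 test is significant when pushing style has no effect (normal approximation).

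| Imbalance × effect | Bias (SD) | Bias in SEs, n = 84 / 105 | False significance, n = 84 / 105 |
|---|---|---|---|
| any × none, or equal use | 0 | 0 / 0 | 5.0% / 5.0% |
| 0.10 × 0.25 | 0.025 | 0.16 / 0.18 | 5.3% / 5.4% |
| 0.20 × 0.50 | 0.100 | 0.65 / 0.72 | 9.9% / 11.2% |
| 0.30 × 0.50 | 0.150 | 0.97 / 1.09 | 16.3% / 19.2% |
| 0.30 × 0.75 | 0.225 | 1.46 / 1.63 | 30.8% / 37.1% |

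Against the implied 0.5 SD, the bias is between 5% (0.025/0.5) and 45% (0.225/0.5) of the difference the study appears sized to detect.

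**4. Cost of adjusting for one recorded binary exposure.** With proportions p1 and p2 and mean p̄, R² = ((p1 − p2)²/4) / (p̄(1 − p̄)), and the variance inflates by 1/(1 − R²). Power is for d = 0.5 and 84 per group, where it is 90.0% without adjustment.

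| Assumed use | R² | Variance factor | Power |
|---|---|---|---|
| 30% vs 40% | 0.011 | 1.01 | 89.7% |
| 30% vs 50% | 0.042 | 1.04 | 88.7% |
| 20% vs 50% | 0.099 | 1.11 | 86.8% |

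The loss is about 3 points at most in these scenarios. The calculation gives no credit for residual variance that the covariate may explain, and it covers one exposure, not all three together.

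**The case against.** The other side has several good arguments.

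- **The list is not the form.** The Case Report Form section lists effectiveness outcomes, where exposures would not be expected. The list is also incomplete: Survey for Women says that withdrawal notes go on the form too. A reader might infer that these treatments are not on the form at all. A condensed article with the form not shown does not support that; they are only absent from the items listed.
- **Silence is not permission.** A reader might infer that oxytocin and other analgesia are allowed in both cohorts. The article neither allows nor excludes them, and the uncomplicated-labor criteria may remove some such women. How many cannot be known from the text.
- **The epidural rationale is not simply inconsistent.** Principal Findings cites a definition of normal birth "without any surgical, medical, or pharmaceutical intervention", which is wider than the exclusion of women "administered epidural analgesia". The same section, however, gives a reason specific to epidural: "women who used epidural analgesia during labor may have difficulty feeling their pushing instinct, and hence, they are excluded from this study". The title, objectives and conclusions already describe the population as without epidural, so no relabelling is needed.
- **The confounding is not irreparable.** A reader might conclude that duration is compromised for good. Participants says that "age and the parity and labor care section of the medical notes will be reviewed and examined and parity in 2 cohorts will be matched". What is charted there can be extracted for both cohorts.
- **Not all oxytocin is a baseline factor.** If first started during the second stage, it may respond to slow progress and so result from pushing style. Conditioning on it could remove part of the effect or add bias.
- **Size and rank.** The magnitudes are assumed, the design is openly nonrandomized, and duration is secondary.

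All of this narrows the point. It does not remove it, because the matching variable and the unadjusted tests are stated positively, and nothing in the article names these co-treatments for reporting or adjustment.

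**Conclusion.** The point holds as a limited one. Following the article as written leaves second-stage duration open to confounding by induction, oxytocin and non-epidural analgesia, in a comparison that controls for parity alone beyond the shared eligibility criteria. Direction is unknown. Size, on assumed inputs only, runs from negligible to about one standard error or somewhat more (at most 1.6 over the range tried). No imbalance is documented, and with equal use there is no bias. What is at stake is the secondary, exploratory objective and any estimate of difference carried into the future trial. The primary feasibility and acceptability outcomes are not touched.

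**What to change.** 1. From the labor care notes of both cohorts, extract: induction (yes/no); oxytocin started before full dilation (yes/no); non-epidural analgesia before the second stage (type).
2. Report the balance of these by cohort.
3. Present the difference in duration adjusted for parity and these pre-second-stage exposures, beside the unadjusted result.
4. Record oxytocin first started during the second stage as a separate item and report it descriptively. Do not match, stratify or adjust on it.

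Whether any of these treatments should be permitted is for the investigators and is not part of this point.

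The cost is a little more extraction time and a small loss of precision. The fix depends on the items being charted. The Results section says that data collection ended in October 2023, so if they were not taken then, the notes must be reopened, which for the deidentified comparison notes requires that the same records can still be found.

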### Intervention

#### Preparation Program for Midwives

Before the commencing of the study, a preparation program will be provided to the recruited 6 midwives. The program was developed and informed by the research team’s midwifery experience, engagement with the literature and a systematic review [8].

The aim of the midwifery preparation program is to provide midwives with comprehensive and evidence-based practice information on the management of pushing in particular the management of spontaneous pushing during the second stage of labor. This will ensure that midwives feel confident to support women with spontaneous pushing during the second stage of labor. The program will run over 3 weeks and will include 6 sessions, and 5 hours in total over 3 weeks. The training plan is displayed in Table 4.

**Table 4 table4:** Preparation program for midwives.

Week and session		Topic	Details	Duration (min)

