#### Strategies to Support Spontaneous Pushing During Labor

Spontaneous pushing encourages a woman to push following her bodily instincts. A standardized step-by-step procedure may not be suitable for every laboring woman. The following strategies are shown to facilitate the spontaneous pushing during labor: (1) encourage woman to select the most comfortable position for her during pushing [7]; (2) offer information about progress of her labor and about any sensations she may feel [25]; (3) affirm to the woman how well her body is working and encourage her to work with and listen to her body urges [25]; (4) support the woman to wait for pushing urges, instead of coaching her to push immediately when the contraction begins [25]; (5) support the woman to push with open glottis, including sighing, moaning, or even crying [26]; and support and encourage the woman to give several short pushes (usually 4 to 6 s) instead of 1 long push (8 to 10 s or even longer) [27].

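### Maternal pushing position is listed as an effectiveness outcome, but the routine notes that supply the comparison cohort do not routinely record it

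*Protocol article*

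**What the plan says.** The Secondary Outcomes section puts position among the effectiveness outcomes: "Secondary outcomes will include the duration of the second stage of labor, maternal pushing position, mode of birth", followed by the other maternal and neonatal items. The Case Report Form section repeats the list as items that the researcher extracts from a woman's medical notes.

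The same section then gives the limitation, "As the maternal pushing position is not routinely recorded in medical notes", and two remedies. The researcher "will ask the midwife about a woman’s pushing position during labor and will record it on the CRF". In addition, "Midwives will also be advised to record the maternal pushing position in the labor notes during the preparation sessions". Those sessions have a defined audience: "a preparation program will be provided to the recruited 6 midwives".

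The Participants section describes the comparison cohort as 105 sets of deidentified notes from women who had directed pushing and who are not themselves recruited. Information from these notes is to be used to compare health outcomes between the cohorts. The Results section also says that labor and birth outcomes will be compared.

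The section on strategies to support spontaneous pushing begins its list with this one: "encourage woman to select the most comfortable position for her during pushing". Table 5, which assigns an analysis method to the secondary outcomes, has no row for position.

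**The concern.** A between-cohort comparison needs the outcome measured in the same way, and in enough women, on both sides. Here the protocol identifies an item that its main data source does not routinely hold, and the remedy it describes works on one side only. Three consequences follow.

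- **Missingness.** The control value is likely to be absent from most audited notes.
- **Differential ascertainment.** The intervention value comes from a midwife's answer to a direct question. The control value, where there is one, comes from whatever was charted. Notes that mention position may be atypical, so an available-case comparison would be selective as well as sparse.
- **Interpretation.** Support for free choice of position is part of what the intervention cohort receives. A difference in position would partly show that the intervention was delivered, and could not be read simply as its effect.

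At stake is one secondary, exploratory result. A table with position in two columns would also obscure something useful for the future randomized trial: whether the item can be obtained from routine notes at all.

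**Working it through.** **1. Sources side by side**

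| | Intervention cohort | Comparison cohort |
|---|---|---|
| Women | 105, recruited | 105 sets of notes, women not recruited (Participants) |
| Routine notes hold position? | Not routinely (Case Report Form) | Not routinely (Case Report Form) |
| Midwife asked? | Yes; the sentence directly follows the one on logging the midwife who supported the recruited woman | No provision stated; notes are deidentified |
| Midwife advised to chart it? | Yes, the 6 midwives in the preparation program | Only if one of those 6 happened to give the care |

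The third and fourth rows are where the cohorts part. Nothing in the document supplies a substitute source for the right-hand column.

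**2. The plan's own figure**

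The 105 per group is based on the duration of the second stage. Effect size, SD and noninferiority margin are not given, so the figure cannot be reproduced. This point does not depend on it, and 105 is used below only as the number of audited notes.

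**3. Illustration of size**

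Let r be the share of control notes that record position. The document gives no value, so r is an assumption. Usable controls are m = 105 × r. The 95% half-width around a control proportion of 50% is 1.96 × √(0.25/m). With nothing assumed about the missing notes, the control proportion can lie anywhere in an interval of width 1 − r.

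| r (assumed) | m | Half-width | Width of worst-case bounds |
|---|---|---|---|
| 0% | 0 | undefined | 100 points |
| 5% | 5.25 | 1.96 × √(0.25/5.25) = 43 points | 95 points |
| 10% | 10.5 | 1.96 × √(0.25/10.5) = 30 points | 90 points |
| 20% | 21 | 1.96 × √(0.25/21) = 21 points | 80 points |
| 50% | 52.5 | 1.96 × √(0.25/52.5) = 14 points | 50 points |
| 100% | 105 | 1.96 × √(0.25/105) = 10 points | 0 |

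The half-width covers sampling error only. It takes the recorded notes as a random sample of all control notes, which sporadic charting does not guarantee. The last column shows how much more is open without that assumption.

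**The case against.** The strongest reply has four parts.

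- **Not routinely recorded does not mean never recorded.** This stands. A reader might infer that the comparison is empty or that close to 100% of control values are missing. The text does not support that. Some notes may hold the item, and the document gives no rate.
- **The remedy is not expressly confined to recruited women.** Control notes are identified over the same period, and the Strengths and Limitations section accepts that trained midwives may care for routine-practice women. Some charting in controls is therefore possible. But such notes would come from the midwives for whom that section raises the risk of crossover, so they would be a poor basis for the comparison.
- **No analysis of position is fixed, and it could fairly be described as an outcome.** Table 5 indeed has no row for it. The outcome lists and the stated plan to compare the cohorts still include it. Calling it a process measure is a judgement, though it rests on the protocol's own list of strategies.
- **It is only secondary.** This stands, and it limits the weight of the point.

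A reader might also infer a bias in neonatal intensive care transfer, because Table 2 ticks the case report form at "Visit 4: within 2 hours after birth" while the outcome, "Newborn transferred to the neonatal intensive care unit because of any emergency", has no time window. The documents do not establish this. The tick is a scheduling mark for a form filled from the notes. The Survey for Women section has withdrawal notes entered on the form, so it may well stay open. No passage says that later transfers are ignored. On the control side, the Participants section describes a review of the labor care section, not of complete notes to discharge. Any figure for such a bias would rest on assumed transfer rates and on a difference inferred from silence; if both cohorts are read over the same period, the bias is zero.

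**Conclusion.** The point holds for maternal pushing position alone. On the protocol's own words, the item is an effectiveness outcome, routine notes do not routinely hold it, the remedy is tied to the recruited women and their midwives, and the comparison cohort has no other source. The comparison would probably be sparse in controls and would be ascertained differently in the two cohorts.

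Its size depends on the unknown recording rate. Between 5% and 20%, the control proportion would rest on about 5 to 21 women. The conclusion assumes that midwives are asked about recruited women only, which is the natural reading of the Case Report Form section but is not stated outright.

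The weight is modest. Position is secondary in a feasibility study, no success criterion uses it, and the primary feasibility and acceptability outcomes are untouched. No claim is made that neonatal intensive care transfer is biased.

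**What to change.** 1. Take maternal pushing position out of the between-cohort effectiveness comparison, and say so where the secondary outcomes are listed.
2. Report it for the intervention cohort as numbers and percentages, labelled as a process or fidelity measure, with its source stated (midwife report or labor notes).
3. Report how many of the 105 audited notes record position. This tells the planners of the future trial whether they need prospective recording in both arms.
4. As a minor clarification only, state that neonatal intensive care transfer is read over the same period in both cohorts.

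The cost is the loss of one exploratory comparison. The article says that data collection ran from May to October 2023 and that analysis was to finish by May 2024, so the change falls at analysis and reporting. It needs wording and a simple count from notes already under review, with no new contact with women.
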